## Abstract

**Background:**

Opioids are still widely prescribed to long-term pain patients although they are no longer recommended for long-term treatments due to poor evidence for long-term efficacy, risks of serious side effects, and the possibility of inducing opioid hyperalgesia. In a Cochrane study from 2017, the authors identified an urgent need for more randomized controlled trials investigating the efficiency and effects of opioid tapering.

The study aimed to assess (1) the efficiency of a structured intervention in causing stable reductions of opioid consumption in a population with long-term non-malignant pain and (2) effects on pain, pain cognitions, physical and mental health, quality of life, and functioning in response to opioid tapering.

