### Objectives {7}

Primary objective: To determine if tapering of medically prescribed opioids in a long-term non-cancer pain population is superior to control in reducing dispensed opioids and non-inferior regarding participants’ report on pain, pain cognitions, physical and mental health, quality of life, and functioning.

Secondary objective: To determine if a reduction in opioid intake displays stability over time.

Research hypothesis: Tapering of opioids in a structured intervention will reduce opioid intake by at least 50% and is superior to controls in reducing dispensed opioids.

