### Trial design {8}

The design of the present study is an RCT, which is under recruitment and conducted among patients with long-term pain who have been accepted to undergo a structured intervention aiming to taper opioid long-term treatments. The study population will be randomly allocated to either (1) the start of tapering opioids immediately or (2) the control group who will return to usual care and commence tapering of opioids 4 months later. A 12-month follow-up after the start of the intervention is included (Fig. 1). The study lies within a superiority framework. Primary endpoints are hypothesized to generate a decrease in opioid use in comparison to controls.

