### Sample size {14}

A “responder” to treatment is a participant who experiences at least a 50% reduction in opioid consumption [28]. Estimation of sample size was based on an effect size of 0.5 (Cohen’s *d*) 80% power, *α* = 0.05, and drop-off at 10%. The results from the calculation indicated the need for 70 individuals in each group.

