## Statistical methods

### Statistical methods for primary and secondary outcomes {20a}

All statistical analyses will be performed with the SPSS software (version 25, IBM Inc). Continuous data will be expressed by means, standard deviation and 95% confidence interval, and categorical data in numbers and percentages.

The intervention arm (tapering opioids) will be compared with control (waiting list) for primary and secondary outcomes at 4 months of follow-up. Statistical analysis of differences between groups will be performed per protocol (attending follow-up 4 months after the start of the intervention and attending second baseline visit in controls) with a paired *t*-test regarding the primary outcome and a Wilcoxon signed-rank test regarding secondary outcomes.

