### Methods for additional analyses (e.g., subgroup analyses) {20b}

#### Retention to intervention at 12 months

Analysis of retention to the tapered dose will be performed with a paired analysis within the allocated group. Changes in percent from the time point for follow-up after the received intervention at 4 months (intervention) or 8 months (control) will be calculated. The analysis will be performed with repeated measures ANOVA.

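### The stability objective is matched to a repeated measures ANOVA, which tests for change and gives no basis for concluding that the opioid reduction is stable

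*Protocol article*

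**What the plan says.** The Objectives section states: "Secondary objective: To determine if a reduction in opioid intake displays stability over time". The abstract puts the same idea into the first aim, which is to assess "the efficiency of a structured intervention in causing stable reductions of opioid consumption".

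The analysis is given under Methods for additional analyses {20b}, Retention to intervention at 12 months, in three sentences:
- The first sets the comparison: "Analysis of retention to the tapered dose will be performed with a paired analysis within the allocated group".
- The second defines the variable as percent change since the post-taper visit, which falls at month 4 in the intervention arm and month 8 in controls.
- The third names the test: "The analysis will be performed with repeated measures ANOVA".

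Three other places bear on the point.
- Statistical methods {20a} says of all continuous data: "Continuous data will be expressed by means, standard deviation and 95% confidence interval".
- Sample size {14} defines a responder as a "participant who experiences at least a 50% reduction in opioid consumption". The research hypothesis uses the same 50%. Neither place links it to retention at month 12.
- Trial design {8} says "The study lies within a superiority framework" and makes no exception for stability.

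The protocol states no acceptable size of rebound and no rule for concluding that the reduction is stable.

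**The concern.** A reduction is stable if the dose does not rise materially once the taper is over. That is a one-sided claim that change is small enough, and a further fall would not count against it. Repeated measures ANOVA has equal means over time as its null, so its only positive conclusion is that the dose changed.

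- **A non-significant result** shows only that change was not detected. Fewer or noisier data make it more likely.
- **A significant result** does not settle the question either. The F-test carries neither direction nor size, so a small rise or a further fall can produce it. If baseline is one of the levels, the taper itself will dominate.

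Stability is the whole secondary objective and part of the first aim in the abstract. Controls start tapering at 4 months, so no untapered randomised comparator remains at month 12 to check the within-arm conclusion. This is a mismatch between a named objective and a named test. It would remain if every taper had ended by the post-taper visit.

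**Working it through.** **1. Number analysed.** Sample size {14} gives d = 0.5, 80% power, α = 0.05 and 10% drop-off. Two-sided, n = 2(1.960 + 0.842)²/0.5² = 62.8, so 63 per arm, and 63/0.9 = 70. The stated 70 per arm reproduces. It is sized for a between-group difference at 4 months and not for stability. I use 63 as the number analysed per arm.

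**2. Assumptions.** The protocol gives no SD of change from the post-taper visit to month 12, so I take 20, 30, 40 and 50 as a range. Change is in percentage points of the pre-taper dose. The protocol's own variable is percent change from the post-taper visit, so these figures illustrate the problem and do not size it on the written scale. The true mean rise is set at 10 points, one fifth of the 50-point responder reduction.

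**3. How often the test misses that rise.** With one within-arm contrast (post-taper visit against month 12), repeated measures ANOVA equals a two-sided paired t-test. The probability of non-significance comes from the noncentral t with 62 degrees of freedom and noncentrality (10/SD)·√63.

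| SD of change | Noncentrality | P(non-significant), n = 63 |
|---|---|---|
| 20 | 3.97 | 3% |
| 30 | 2.65 | 26% |
| 40 | 1.98 | 50% |
| 50 | 1.59 | 65% |

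With 50 analysed, the figures at SD 30, 40 and 50 are 36%, 59% and 72%. Losing participants makes the apparently reassuring result more likely.

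**4. The alternative rule.** Declare stability only if the one-sided 95% upper limit for mean change lies below a limit L. When the true rise equals L, this wrongly declares stability 5% of the time, whatever the SD (for approximately normal means).

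Its cost appears when the true change is zero. The distance from the mean to the upper limit is 1.670·SD/√63. The chance of declaring stability is the probability that the observed mean plus this distance falls below L. L = 10 is for illustration only.

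| SD of change | Mean to upper limit (points) | P(declare stable), true change 0, L = 10 |
|---|---|---|
| 30 | 6.3 | 83% |
| 40 | 8.4 | 62% |
| 50 | 10.5 | 47% |

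**The case against.** The strongest reply has five parts.

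- **The plan never says that a non-significant ANOVA means stable.** This stands. The objective is to determine whether the reduction is stable, not to show that it is. A reader might infer that the sponsor intends to read no significant change as stability, but no sentence says so.
- **Estimation is already planned.** This stands in part. Percent changes and 95% intervals would show the size, direction and uncertainty of any rebound. A reader might therefore infer that the trial cannot inform stability at all, and that goes too far. What is missing is a criterion against which to judge the estimate.
- **A limit and a decision rule can be left to the analysis plan, which is not shown.** The absence of a limit alone would not be a finding. But the article has already chosen the inferential method for this objective, and that method does not fit it.
- **The ANOVA levels are not stated.** True. If baseline is included, a baseline-to-month-12 contrast would test whether some reduction persists. That is a different question from whether the post-taper dose is held, and the section's reference to retaining the tapered dose points to the latter.
- **The magnitude depends on assumed SDs and a different scale.** This also stands. The 10-point miss rate runs from 3% to 65% across the range, so it shows what could happen and does not measure a defect.

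**Conclusion.** The point holds in a limited form. The protocol sets stability as its secondary objective and names, as the only inferential method, a within-arm test for change that offers no basis for a positive stability conclusion. The planned percent changes and intervals describe any rebound but are tied to no criterion. The primary 4-month comparison is unaffected.

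The illustration of 3%, 26%, 50% and 65% rests on 63 analysed per arm, a single paired contrast, assumed SDs of 20 to 50, and change scaled to the pre-taper dose. At a small SD the practical risk is slight. At SD 40 or more, a 10-point mean rise would go undetected at least half the time. The change is worth making before the final register data are drawn.

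**What to change.** In the Retention to intervention at 12 months section (or the analysis plan):

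1. Base the stability conclusion on the estimated mean change in register MME from the post-taper visit to month 12, scaled to the pre-taper dose, with its one-sided 95% upper confidence limit (by bootstrap if the changes are skewed).
2. Conclude stability only if that limit lies below a maximum acceptable rebound, which the sponsor sets and justifies before the final register extract is drawn. The 10 points used above are not a proposal.
3. Report, with a 95% CI, the share of participants with at least a 50% reduction at the post-taper visit who still meet that criterion at month 12.
4. State that a non-significant ANOVA will not be interpreted as stability.
5. Make the dose windows comparable for this contrast. Primary outcomes {12} uses 30 days for the 4-month dose and 90 days for the 12-month dose.

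The cost is a few sentences and one justified limit, with no new data or participants. There are two downsides. With a large SD the trial may be unable to declare stability even when there is no rebound, as the 62% and 47% above show. Also, the limit can be fixed before the final extract but not fully blind to outcome: the trial is open, self-reported dose is collected at visits, and prescribers may consult the register during the trial.

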### Methods in analysis to handle protocol non-adherence and any statistical methods to handle missing data {20c}

When calculating total scores of TSK, PCS, CPAQ-8, HADS, and RAND-36, missing values may occur. These will be managed in accordance with guidelines from SQRP’s Clinical Data Management team. These are:
TSK: two missing values are replaced by, at the individual level, the mean score for all replies of the instrument. More than two missing values are not allowed.PCS: two missing values are replaced by, at the individual level, the mean score for all replies of the instrument. More than two missing values are not allowed.CPAQ-8: no missing values are allowed.HADS: two missing values are allowed in each subscale anxiety and depression. Two missing values for each subscale are replaced by, at the individual level, the mean score for all replies of the subscale. More than two missing values per subscale are not allowed.RAND-36: missing values in each subscale are considered. Half the reported questions + one must occur if a total score is to be reported from a subscale. Missing values are replaced by the mean value of the remaining scores in the current subscale.

### Plans to give access to the full protocol, participant-level data, and statistical code {31c}

The data that supports the findings of this study are available from SQPR and SDPR, but restrictions apply to the availability of these data, which were used under license for the current study, and so are not publicly available. Data are, however, available from the authors upon reasonable request and with permission of SQPR and the Swedish drug register of the National Board of Health and Welfare. There is no plan to grant public access to the final dataset.

All authors will have access to the final coded trial dataset.

## Oversight and monitoring

### Composition of the coordinating center and trial steering committee {5d}

Pain Rehabilitation Clinic of Skane University Hospital in Lund will coordinate the trial. Organizational support to Pain Centre Sahlgrenska University Hospital in Gothenburg and Pain and Rehabilitation Centre in Linköping will be provided. Meetings between centers will take place once every second week to monitor the recruitment of participants, implementation of the intervention, and any problems in data collection [52].

### Composition of the data monitoring committee, its role, and reporting structure {21a}

No data monitoring committee is needed as the trial is not considered a drug trial.

Capturing of primary and secondary outcomes already has routines of SDPR and SQRP.

### Adverse event reporting and harms {22}

Adverse events are recorded and addressed (see also the “Strategies to improve adherence to interventions {11c}” section) for all participants during the trial and will be documented. Discontinuation might be called upon due to the need for specialized addiction care.

### Frequency and plans for auditing trial conduct {23}

No auditing is planned.

### Plans for communicating important protocol amendments to relevant parties (e.g., trial participants, ethical committees) {25}

Any modifications to the protocol which may impact on the conduct of the study and the potential benefit of the patient or may affect patient safety, including changes of study objectives, study design, patient population, sample sizes, study procedures, or significant administrative aspects, will require a formal amendment to the protocol. Such amendment will be approved by the Ethics Committee and changes in trial registration at ClinicalTrials.gov will be performed.

## Dissemination plans {31a}

All authors agree to disseminate the results from TOPIO regardless of its results. Dissemination will be through journal publication.

## Discussion

As described in the “Introduction” section, the problem of long-term opioid prescription periods and health care professionals feeling lost when it comes to helping their patients to discontinue treatments is significant. The present study could possibly give insights into the efficiency and effects of opioid tapering that could aid health professionals and patients and possibly facilitate attempts to taper opioid treatments. In order to have an impact, i.e., to facilitate dissemination, we wanted to perform this study as a well-described but straightforward physician–nurse collaboration without adding any specific psychotherapeutic techniques. In our opinion, this is crucial for this particular branch of health care to improve with possible benefits for both individuals and society such as reduced risks of developing substance use disorders and fatal overdoses.

## Trial status

The first participant was recruited in March 2018. To date, 62 patients are allocated to the intervention or control group. At this rate, the allocation process is assumed to proceed until 2024 to reach the goal of 140 randomized participants. With additional trial sites being added in 2021 and 2022, the recruiting process may end earlier. During the 2025 follow-up, data processing and manuscript preparation are planned.

The current version of the protocol: Clinical Trials.gov PRS 06/22/2021 by [name], not yet publicly released.

Due to the COVID-19 pandemic, the recruitment process was brought to a halt in March 2020 and resumed on 1 September 2020 without any changes of the study population, but with an option for participants to take part in follow-up after intervention fully by phone or video. During January 2021, a halt in recruitment again took place for 1 month. Due to the COVID-19 pandemic, follow-up visits have been performed mostly by phone. Elderly, beyond the age of 70, was not allowed to enter into the trial between 7 January and 7 June 2021.

## Data Availability

Lund University Hospital is the trial sponsor with the main collaborator Lund University. No one outside the group of researchers will be involved in the data collection, analysis, interpretation, or writing the present manuscript. All authors will have access to the final coded trial dataset.

## Abbreviations

CPAQ-8: Chronic Pain Acceptance Questionnaire
HADS: Hospital Anxiety and Depression Scale
MME: Milligram morphine equivalent dose per day
NPRS: Numeric Pain Rating Scale
PCS: Pain Catastrophizing Scale
PEth: Phosphatidylethanol 16:0/18:1
RCT: Randomized controlled trial
SPDR: Swedish Prescribed Drug Register
SQRP: Swedish Quality Registry for Pain Rehabilitation
SUD: Substance use disorder
TSK: Tampa Scale of Kinesiophobia
